## Abstract

Evidence reports positive effects of neck motor control and aerobic exercises (AEs) to improve pain in individuals with temporomandibular disorders (TMD) and neck pain. A single bout of exercise typically leads to an increase in pain thresholds up to 30 min post‐exercise, known as exercise‐induced hypoalgesia (EIH). Studies evaluating the effects of aerobic and neck motor control exercises on EIH in individuals with chronic neck pain and TMD are limited. Measuring treatment effects and determining the clinical significance based on exercise types and loads and EIH response can improve clinical outcomes and adherence to exercise programmes. This study was designed to determine the clinical significance of EIH after neck motor control and aerobic training in participants with TMD and neck pain. Participants between 18 and 60 years with neck pain and/or TMD will be randomized to neck motor control or aerobic training groups. Participants will be assessed before, immediately after and 15 min after three treatment sessions within a 12‐week exercise programme. Assessments will include pain intensity, pressure pain thresholds and tolerance of masticatory and neck muscles, and the Global Rating of Change Scale. EIH response will be calculated in absolute and relative changes by subtracting the post‐ from the pre‐exercise values. Distribution‐based (e.g., effect size) and anchor‐based (e.g., receiver operating characteristics) methods will be performed to determine the clinical significance of EIH (minimal important difference).

## INTRODUCTION

1

Musculoskeletal disorders are among the most costly health problems and are the leading causes of disability (Vos, 2012). One example is temporomandibular disorders (TMD), which are frequently associated with headaches and neck pain, and constitute a large part of public health expense (Vos et al., 2017). In addition, neck pain is the 11th leading cause of years lost to disability (Abbafati et al., 2020). Individual, ergonomic, sociocultural and psychosocial risk factors contribute to neck pain occurrence and chronicity (de Melo Castro Deligne et al., 2021). A high comorbidity between TMD and neck pain has been reported, mainly due to the close relationship among the neck, orofacial and cranial regions, with about 70% of patients with TMD reporting neck complaints (de Oliveira‐Souza et al., 2020; Silveira et al., 2015).

Neck muscle exercises are effective in reducing painful symptoms related to TMD (Armijo‐Olivo et al., 2016) and neck pain (Falla et al., 2013; Ris et al., 2016). Specific neck training using motor control exercises reduces the risk of neck pain recurrence and improves muscle strength, endurance, range of motion and neck motor control (De Pauw et al., 2019). Such effects are likely driven by physiological and biomechanical factors (Gross et al., 2015).

In addition, whole‐body exercises could reduce pain in patients with chronic pain conditions (Geneen et al., 2017). Previous studies reported that aerobic exercises (AEs) improve the quality of life and mental health of individuals with fibromyalgia, obesity, depression and headaches (Ambrose & Golightly, 2015; Ferro Moura Franco et al., 2021), and that a large number of individuals with TMD are sedentary or irregularly active (Tavares et al., 2024). Regular exercise, especially AE (i.e., an exercise subtype targeting large muscle groups and performed over an extended period of 20–60 min), promotes pain relief potentially by increasing serotonin and opioid levels in central pathways involved in the modulation of nociception (Lima et al., 2017; Rice et al., 2019; Stagg et al., 2011). However, limited evidence is reported on the effects of AEs on pain in individuals with both TMD and neck pain (de Oliveira‐Souza, Gülker, et al., 2024, 2024, de Oliveira‐Souza, Kempe et al. 2024, 2024). Therefore, a multimodal treatment including aerobic and strengthening exercises could improve the pain and function of individuals with craniocervical pain (Booth et al., 2017).

In pain‐free populations, a single session of exercise (e.g., aerobic, isometric, dynamic) typically leads to an increase in pain thresholds that can last up to 30 min, known as exercise‐induced hypoalgesia (EIH) (McPhee Christensen et al., 2022; Moana‐Filho et al., 2018; Nasri‐Heir et al., 2019; Wewege & Jones, 2021). Several mechanisms may contribute to EIH, including the activation of the opioid and cannabinoid systems, release of hormones and neurotransmitters (e.g., endorphins, enkephalins) in response to induced stress, changes in the cardiovascular system, and pain modulation by the central nervous system (De la Corte‐Rodriguez et al., 2024; Vaegter & Jones, 2020). A single session of isometric, submaximal aerobic, and range of motion exercises reduces local (painful area) and remote (non‐painful area) pain sensitivity in individuals with chronic neck pain (Senarath et al., 2023). However, submaximal AEs have only been evaluated in chronic whiplash disorders, and the meta‐analysis included only observational studies (Senarath et al., 2023), meaning that clinical trials evaluating the effects of aerobic and specific exercises on EIH in individuals with chronic neck and TMD pain are limited, with low quality of evidence and uncertain risk of bias (Wewege & Jones, 2021). Another review stated that despite several studies being conducted on EIH in different chronic conditions, only a minority used randomized controlled trial designs (Vaegter & Jones, 2020).

Moreover, identifying which exercise parameters yield the strongest hypoalgesic effects can help clinicians to choose the best intervention approaches. In this context, the concept of clinical significance is highly important to understand and interpret the results of clinical research. Clinical relevance or significance is roughly defined as the value or importance of the effect of an intervention based on the patient's perspective (Armijo‐Olivo et al., 2022). In this scenario, the patient's perception regarding changes after treatment can be more meaningful than the statistical result (i.e., a statistically significant result does not guarantee clinical improvement). Thus, measuring the clinical significance of an intervention and tailoring the intervention based on EIH response can benefit clinical settings, and improve adherence to exercise programmes, which is a challenge in chronic pain populations (Ambrose & Golightly, 2015). However, the reporting of clinical significance in rehabilitation studies for individuals with chronic pain is still insufficient (Armijo‐Olivo et al., 2022). Furthermore, the need to establish the minimal important difference (MID) of EIH, to ensure blinding of assessors, and to consider patients expectations regarding the treatment when evaluating EIH has been highlighted in the literature (Aron et al., 2024).

In this context, an underestimation of the acute effects of physical activity on managing chronic pain has been reported (Schofield et al., 2011). Thus, it is important to explore how a single bout of exercise affects pain and the clinical significance of EIH in individuals with neck pain and TMD. Therefore, this study was designed to fill in this gap.

## OBJECTIVES

2

To evaluate whether a single session of neck motor control exercises and aerobic training can cause EIH by measuring pain intensity, pressure pain thresholds (PPT) and tolerance (PPTo) in individuals with TMD and neck pain.

To evaluate EIH response at different time points during a 12‐week progressive neck motor control exercise and aerobic training treatments.

To determine the clinical significance of EIH, by calculating the MID of it based on distribution and anchor‐based methods.

## METHODS

3

### Study design

3.1

This study will be a parallel pilot randomized controlled clinical trial conducted at the University of Applied Sciences, Osnabrück, Germany. This study will be part of an umbrella project and will include participants recruited from a larger study previously registered in clinicaltrials.gov (NCT05232604). This project has also been approved by the human research ethics committee of the University of Applied Sciences (HSOS/2020/2/1) and will be conducted in accordance with the ethical principles of the *Declaration of Helsinki*. Figure 1 details the overall study period of enrolment, assessments and interventions. This protocol follows the guidance of the Standard Protocol Items: Recommendations for Interventional Trials (SPIRIT) statement.

**FIGURE 1 eph13772-fig-0001:**
[figure not shown]
Schedule of enrolment, interventions and assessments. CSI, central sensitization inventory; PAR‐Q+, Physical Activity Readiness Questionnaire.

### Participants

3.2

Women between 18 and 60 years of age, diagnosed with chronic non‐specific neck pain (as described by the IASP) and/or diagnosed with TMD according to the Diagnostic Criteria for Temporomandibular Disorders—DC/TMD (Dworkin, 2014) will be included. In addition, a baseline pain score of at least 30 points on a 0 to 100 visual analogue scale (VAS) will be required. Participants with severe pathologies (red flags) related to neck pain, reporting comorbidities (e.g., fibromyalgia), diagnosed with psychiatric disorders, and/or who received therapy within 3 months before study entry will be excluded. All participants will complete the Physical Activity Readiness Questionnaire (PAR‐Q+) to assess readiness to exercise. The Central Sensitization Inventory (CSI) recommended for patients with chronic pain will also be applied. The CSI is an easy‐to‐apply self‐report questionnaire that tracks and assesses symptoms related to overall sensory disturbances (Mayer et al., 2012).

This exploratory clinical trial aims to gather preliminary data on the safety and potential efficacy of a single bout of exercise for individuals with TMD and neck pain. Given the exploratory nature of this study, a formal sample size calculation was not conducted. Instead, the sample size was determined based on practical and logistical considerations. This exploratory study pilot will initially target 30 participants (15 per group), aiming to gain insights and assess feasibility. Based on the targeted sample size and a clinically important difference of 19 points (on a 0–100 pain scale) (Calixtre et al., 2020) with a standard deviation of 20, the study has an estimated 71% power to detect a large effect size (ES, Cohen's *d* = 0.95) using a significance level of 0.05. The recruitment rate of participants, availability of the research team, time, and resources were considered for the targeted sample size. The data collection is expected to be finished by the end of 2025. The results of this study will help to design and calculate sample sizes for future studies.

### Allocation concealment

3.3

All participants will be randomly assigned to one of the treatment groups: neck motor control exercises or AEs by using an automated system hosted on a web platform. The randomization sequence will be stratified by chief complaint (neck pain or jaw pain) and age (18–30, 31–45, 46–60) and generated by an external party using a randomization website. The sequence generated will be automatically programmed in REDcap to allow the allocation concealment of the sequence.

### Treatment interventions

3.4

#### Aerobic exercise (AE)

3.4.1

AE training will consist of 12 weeks of exercise supervised by a physiotherapist with a frequency of three times per week (36 sessions in total). Overall, the session will have a total duration of 60 min and will be divided into three parts: warm‐up, main exercise period and cool‐down. The training will be performed on a cycle ergometer or treadmill (based on the participant's choice). The intensity will be based on maximum heart rate (HR_max_), heart rate reserve (HR_res_) and the subjective perception of effort (Borg Scale), which will be monitored. The Borg scale will be the main variable considered to increase the intensity of the protocol or to stop the training. The HR_max_ will be calculated by a ramp protocol for the cycle ergometer and confirmed by standard formulas.

The intensity of the AE programme will be progressively increased according to each participant's response but will be standardized as much as possible, as follows:
In the first 2 weeks, participants will start the walking/cycling programme at low intensity (at 60% HR_max_ or 9–11 on the Borg scale).At 2–6 weeks, depending on the response to the first sessions, the training will progress to moderate intensity (55–70% HR_max_ or 12–14 on the Borg scale);In the last 6 weeks, high‐intensity interval training (HIIT) will be targeted as recommended by the literature (Geneen et al., 2017). The HIIT consists of changing between moderate and high intensity for short intervals. Thus, during the first 4 min, the participant should train at high intensity (75–90% HR_max_ or 15–17 on the Borg scale), and in the subsequent 3 min, the participant should train at moderate intensity (55–70% HR_max_ or 12–14 on the Borg scale). This is done continuously until the total training time is completed (4 min × 4 times (high‐intensity training) followed by 3 min of moderate in between, totalling 28 min of active training) according to the participant's response. The intensity of the aerobic training in each session will be targeted individually with an increase of 5 W every 5 min according to the specific stage the participant is in and based on the Borg scale. Supplementary Material 1 describes the full protocol for the aerobic training group, which will also perform stretching exercises before and after the intervention.

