#### Neck motor control exercises

3.4.2

The duration will consist of 12 weeks with a frequency of three times per week in the first month, two times in the second month, and once per week in the final month (24 sessions in total). Each session will include localized motor control of neck flexors and extension muscles with a duration of 30–45 min. Low‐load craniocervical exercises (head nods) will be performed in the early stages (first 6 weeks) guided by visual feedback from a pressure unit (NOD device). Higher load neck exercises will be performed in later stages (last 6 weeks). This duration of treatment is commonly used in clinical settings and has been shown to be sufficient to improve clinical outcomes (Bednarczyk et al., 2024). This exercise protocol is detailed in Supplementary Material 2 and has been successfully tested in subjects with neck pain.

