#### EIH procedures and time points

3.5.1

On the days of assessments, participants will be instructed to refrain from additional physical exercise, caffeine, nicotine and alcohol (Vaegter et al., 2019). To evaluate the acute effects of exercise protocols, participants will be assessed before, immediately after and 15 min after a single intervention session. The sessions are part of a 12‐week exercise programme. Since both protocols progressed from light to high intensity throughout the intervention period, three time points (i.e., three sessions) were chosen for the evaluations of three different exercise intensities (low, moderate and high). For the neck motor control exercises group, sessions 3, 12 and 22 were chosen. For the AE group, sessions 3, 12 and 32. Assessors will be blinded to the treatment allocation. Those specific sessions were chosen to ensure that participants will be assessed at the beginning, middle and end of each specific protocol at low, moderate, and high intensities, respectively.

At the three time points, three measurements will be conducted. The first measurement will be collected before the intervention, the second measurement will be immediately after the end of the intervention (considering 5 min of preparation of the room) and the third measurement will be after 15 min of rest on a stretcher (30 min after intervention). During the resting time, no intervention will be performed. Considering that each measurement lasts approximately 15 min, this timeline will allow us to determine whether EIH lasted at least 30–35 min. Figure 2 describes the sequence of events.

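### Heart rate does not separate low from moderate aerobic training, and neck session 12 falls in the low-load stage, so the low/moderate labels of the assessed sessions are only partly supported

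*Protocol article*

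**What the plan says.** Section 3.4.1 (aerobic exercise) sets three stages, each with a heart-rate target and a Borg target joined by 'or':

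- First 2 weeks: "participants will start the walking/cycling programme at low intensity (at 60% HR_max", or Borg 9–11.
- Weeks 2–6: "the training will progress to moderate intensity (55–70% HR_max_ or 12–14 on the Borg scale".
- Last 6 weeks, during the hard intervals: "high intensity (75–90% HR_max_ or 15–17 on the Borg scale".

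The same section bases intensity on HRmax, heart rate reserve and Borg, all monitored, and ranks them: "The Borg scale will be the main variable considered to increase the intensity of the protocol or to stop the training".

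Section 3.4.2 (neck motor control) describes two load stages. Low-load head nods "will be performed in the early stages (first 6 weeks"), and higher-load exercises follow in the last 6 weeks. Sessions are held three times a week in month one, twice in month two and once in month three.

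Section 3.5.1 fixes the assessed sessions at 3, 12 and 32 (aerobic) and 3, 12 and 22 (neck), chosen to represent "three different exercise intensities (low, moderate and high"). It also describes them as the beginning, middle and end of each protocol. For objective 2, section 3.7 fits exploratory mixed models that compare the beginner, intermediate and advanced time points and the two groups.

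**The concern.** The choice of assessed sessions is justified by intensity: session 12 is meant to be a harder bout than session 3 in each arm. The stage definitions do not fully deliver that. In the aerobic arm, a bout at 60% HRmax meets the heart-rate criterion of both the low and the moderate stage. In the neck arm, the stage description puts both sessions in the low-load stage.

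What is at stake is the interpretation of objective 2. If exercise-induced hypoalgesia looks the same at sessions 3 and 12, a reader may conclude that intensity does not matter when the two bouts may not have differed in intensity. If it differs, the difference may be credited to intensity on labels that the section on interventions only partly supports.

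**Working it through.** **1. The plan's own session totals.** Aerobic: 3 per week × 12 weeks = 36, as stated. Neck: 3×4 + 2×4 + 1×4 = 12 + 8 + 4 = 24, as stated. The neck total confirms four-week months, so the session-to-week mapping below uses the plan's own calendar and assumes no missed sessions.

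**2. Stage targets in the aerobic arm (section 3.4.1).**

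| Stage | % HRmax | Borg |
|---|---|---|
| Low | 60 | 9–11 |
| Moderate | 55–70 | 12–14 |
| High | 75–90 | 15–17 |

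- Low against moderate, heart rate: 55 ≤ 60 ≤ 70, so the low target is inside the moderate band. Its position is (60 − 55)/(70 − 55) = 5/15 = 0.33.
- Low against moderate, Borg: 11 < 12, so no value is shared.
- Moderate against high: 70 < 75 on heart rate and 14 < 15 on Borg, so the two are separate on both scales.

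For illustration only, at an assumed HRmax of 180 beats/min the low target is 0.60 × 180 = 108, and the moderate band is 0.55 × 180 = 99 to 0.70 × 180 = 126. At 160 the figures are 96 against 88–112, and at 200 they are 120 against 110–140. The overlap does not depend on the value assumed.

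**3. Stage of each aerobic session** (week = session/3, rounded up). Session 3 is in week 1 (low stage), session 12 in week 4 (moderate stage) and session 32 in week 11 (interval stage). By calendar, the three sessions lie in three different stages.

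**4. Stage of each neck session.** Month one holds sessions 1–12 (weeks 1–4). At two per week, weeks 5–6 hold sessions 13–16. The low-load stage is therefore sessions 1–16 and the higher-load stage is sessions 17–24.

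- Session 3: week 1, low load.
- Session 12: 12/3 = 4, the end of week 4, low load.
- Session 22: month three starts at session 21 (week 9), so session 22 is in week 10, higher load.

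Section 3.4.2 thus supplies two load levels where section 3.5.1 names three, and sessions 3 and 12 share one of them.

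**5. What separates sessions 3 and 12.** Aerobic: Borg and calendar stage, but not heart rate. Neck: nothing in section 3.4.2, which gives no Borg or heart-rate target.

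**The case against.** The strongest reply is that the aerobic stages are separated by the variable that governs them. The Borg bands are disjoint, Borg is named as the main variable for raising intensity, and sessions 3 and 12 fall in different calendar stages. All of this stands. A reader might infer from the heart-rate overlap that the low-versus-moderate contrast is not fixed by the plan at all, or that session 12 could lie anywhere from 5 points of HRmax below session 3 (55 − 60) to 10 above it (70 − 60). The documents do not support that. The contrast is fixed by session number, and the −5 to +10 range would apply only if heart rate alone governed, which section 3.4.1 does not say. What the reply leaves in place is that the only stated physiological criterion with stage-specific values does not distinguish the two stages. Moreover, progression to moderate is conditional on how the participant responds to the early sessions, so the calendar alone does not guarantee it.

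Second, objective 2 is worded by time point, and section 3.5.1 also calls the sessions beginning, middle and end. That is correct, and the model can be fitted as written. But the same section attaches low, moderate and high to those sessions respectively, and it is this label that needs support.

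Third, both arms refer their full protocols to supplementary material that is not shown, where load may be graded more finely. This is possible, but the article's stated figures and labels would still need to agree.

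Fourth, intensity and weeks of training are confounded in any progressive programme. That is true, and reconciling the figures will not cure it. It is another reason for modest wording.

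**Conclusion.** The point holds in a limited form. In the aerobic arm, heart rate does not separate low from moderate, so that label rests on Borg and calendar stage alone. In the neck arm, session 12 is labelled moderate but lies in the same low-load stage as session 3. In each arm the first of the two successive stage contrasts is affected; the step to the last assessed session is not.

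The consequence is confined to how objective 2 is interpreted, in exploratory models within a 30-participant pilot. No endpoint, sample size or power figure changes. The conclusion rests on the article's text, the stated session frequencies with no missed sessions, and supplementary protocols that have not been seen.

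**What to change.** - Reconcile the low and moderate heart-rate figures in section 3.4.1, and the load stages in section 3.4.2, with the low/moderate/high labels in section 3.5.1. Which figures or stages are right is a clinical matter, and none is proposed here.
- Report descriptively, by session, the heart rate and Borg ratings already monitored in the aerobic arm at sessions 3, 12 and 32, so that readers can see whether the stages were distinct in practice.
- Do not enter these values as covariates in the two-arm objective 2 model. Monitoring is stated only for the aerobic arm. Achieved intensity arises after randomisation and is tied to stage by design, so adjusting for it would remove part of the contrast of interest, with about 15 participants per arm.
- Where stages are not separated, label and interpret the contrast as early/middle/late, not as low/moderate/high intensity.

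The cost is wording changes, one descriptive table and a more modest interpretation. No visits, measurements or participants are added.
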